### Interventions

All patients who are included in the RCT will continue to receive CAU according to applicable clinical guidelines during the complete runtime of the study. CAU can consist of psychotherapeutic and/or drug treatment, outpatient, day or inpatient treatment and individual or group treatment.

The main goal of the STAIRS program is to increase the level of functional and personal recovery of patients suffering from the lasting impact of depression on their lives. This will be done with different exercises, by sharing experiences and by providing supportive information. The STAIRS training has a duration of eight weeks, in which participants address the following themes in weekly group sessions: effects of depression and treatment, structure, public stigma and self-stigma, self-image, meaningfulness, connecting to others, relaxation and preventing relapse. Each session will be guided by a clinician (psychologist, nurse practitioner or medical social worker) and a certified expert by experience. Trainers will undergo a 1-day train-the-trainer where the aim of the program and the working methods used are discussed, the complete program is reviewed and example exercises are practised. In between sessions, participants can keep working on a theme via homework assignments on which they will be asked to reflect and interact with each other in a private online community.

Patients in the control condition will receive CAU and some basic psychoeducation. The latter will be delivered in three different information letters (see Additional file 1), which the patients subsequently receive one, four and seven weeks after completing the baseline questionnaires. Each information letter focuses on one of three main aspects of the recovery process: (1) regaining structure in daily life, (2) redefining social relationships and (3) finding a new balance in life. The letters provide basic information about the recovery process, tips on how to cope with depression in everyday life and links to videos, in which peers share experiences regarding the role of the described aspect in their recovery process. The purpose of these letters is to offer practical information on strategies supporting the recovery process, which patients can use as they see fit in their own situation. We find that this intervention can be regarded as a slightly augmented form of CAU. This approach was chosen in favour of delivering only CAU in this group because patients may end their MDD treatment during the study. The psychoeducation letters will offer us the opportunity to keep informing and involving patients and to keep them engaged with the study, even after ending their treatment. At the same time, the added elements are minimal, making sure that the comparison condition is still very close to CAU as it is currently offered in practice.

### Measurements

Quantitative data will be collected by administering online self-report questionnaires in the week prior to the intervention (T0; baseline), the week following the intervention (T1) and 6 months later (T2). Patients can complete the questionnaires at home. A reminder will be sent after three days, and contact will be made by telephone after a week to promote participant retention. In addition to the questionnaires, a short structured interview will be conducted at T2 to assess depressive relapse in the past 6 months. Qualitative data will be collected by conducting semi structured in-depth interviews with a selection of patients from the intervention group, immediately after the end of the STAIRS-program (T1). Figure 2 gives an overview of the planned enrolment, interventions and assessments.

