After informed consent is obtained, patients will be randomly allocated to one of the study arms. Randomization will be performed at the patient level by a research assistant who is not involved in the study, using simple randomization with a 1:1 allocation ratio. A list with 140 randomly generated numbers (0 or 1) will be used to allocate patients in order of the date and time of the informed consent meeting. Patients who are randomized to the active intervention condition will be placed on a waiting list for the treatment in (a) the organization where they received all their previous treatment (for patients referred from organizations that offer the STAIRS training) or (b) in the UCP (for patients who are referred from organizations that do not offer the STAIRS training). The STAIRS training starts when at least three patients have been added to the waiting list. At that time, patients will receive an email inviting them to join the training. This email will contain all needed information about the date and location of the meetings and how to access the private online environment that is used as part of the STAIRS-program. When attending physical meetings turns out to be difficult for participants in the intervention condition, they will be given the option to follow the STAIRS training online. Previous pilot work showed this to be a usable and acceptable option [45].

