This study also has some expected difficulties. First, recruitment may be difficult because of the timing of the interventions in this trial. Patients are recruited during the final phase of their treatment and may therefore be reluctant to participate, as this may feel as a delay of the completion of their treatment. To minimize this risk, we emphasize to patients that STAIRS is an add-on to regular treatment with a specific focus on areas that are considered important by patients themselves in the final phase of treatment. Second, treating clinicians may be reluctant to inform eligible patients about the study because they might have concerns about not being able to end regular treatment during the runtime of the trial. We will therefore emphasize to clinicians that nothing needs to be changed in the current treatment. If the treatment is scheduled for completion during the RCT, this will not change because of participation in this study. Third, because the STAIRS-training is a group intervention, patients assigned to the STAIRS-training have to wait before they can start until enough subsequent patients are randomized to the STAIRS condition to fill up a group. If recruitment is slow, a trade-off may be necessary between reducing the waiting time for patients on the one hand and achieving the target group size on the other. To prevent patients from having to wait too long, a group can start when at least three patients are assigned. However, group dynamics in smaller groups may differ from those in larger groups, which may lead to different results. We will therefore compare the results of different groups based on group size to investigate possible differences. As the group sizes of existing group training programs within mental health care also differ, insight into possible differences can also be helpful when implementing the STAIRS program in daily practice. Last, some patients may be reluctant to join face-to-face group meetings because they feel too exposed or have practical objections, such as excessive travel time. To give these patients the opportunity to participate, the STAIRS program can also be offered online. However, efficacy, patient experiences and cost-effectiveness may differ between the face-to-face and online version of the program. When analysing the data, we will use methods that can account for possible differences between groups, while taking into account a control condition that is ungrouped [81]. Furthermore, the results from the semi-structured interviews will be compared between patients who followed the STAIRS program face-to-face and those who followed the program online. Finally, in addition to overall cost-effectiveness, the cost-effectiveness per program version will also be assessed and compared.

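### In the STAIRS arm the T0 baseline is taken after randomisation and a variable wait, probably with allocation known, so the primary change scores start from a post-randomisation measurement

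*Protocol article*

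**What the plan says.** Recruitment and randomization puts allocation immediately after consent: "After informed consent is obtained, patients will be randomly allocated to one of the study arms". The list is used in order of the consent meetings, and no questionnaire is placed before it. The same section then says: "Patients who are randomized to the active intervention condition will be placed on a waiting list for the treatment". The wait ends when a group can be formed: "The STAIRS training starts when at least three patients have been added to the waiting list". The Discussion confirms the delay: "patients assigned to the STAIRS-training have to wait before they can start until enough subsequent patients are randomized to the STAIRS condition".

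Measurements ties the baseline to the intervention, not to consent or randomisation: questionnaires are completed "in the week prior to the intervention (T0; baseline", again in the week after the intervention (T1), and again six months later (T2). The abstract likewise puts the first assessment at the start of the intervention.

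For controls, Interventions describes three psychoeducation letters, "which the patients subsequently receive one, four and seven weeks after completing the baseline questionnaires". No waiting list or matched delay is described for that arm.

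The primary outcome is the change in the I.ROC, a self-report score with a three-month recall window, from T0 to T1 and from T0 to T2. It is regressed on treatment group (Primary outcome measure; Quantitative analyses).

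**The concern.** Randomisation makes the arms comparable at the moment of allocation. A baseline taken before that moment inherits the comparability; one taken afterwards does not. Here the STAIRS baseline comes after allocation, after a wait that depends on accrual, and at about the time the invitation to the group is sent. Usual care continues meanwhile, so recovery can move between randomisation and T0.

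Three things could then separate the arms before any treatment effect exists. Recovery may not proceed at a constant pace, so a later observation window sees a different stretch of it. Patients who know their arm may answer a self-report questionnaire with anticipation or disappointment. Patients may also leave before T0, and not equally in both arms; the plan excludes nobody and imputes missing values, so someone lost before T0 would be imputed from very little of their own data.

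The Discussion treats the wait as a matter of recruitment and group size, not of the baseline. At stake is whether the change from T0, which carries the primary hypothesis, is a randomised comparison.

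**Working it through.** **1. Order of events.** STAIRS: consent, randomisation, waiting list, group can start, T0, eight weekly sessions, T1, T2. Control: consent, randomisation, T0 at a time the text does not state, letters counted from T0, T1, T2. The STAIRS sequence follows directly from the text. That controls have no delay is inferred from the waiting list being described for one arm only and the letters running from T0.

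**2. The plan's own figure.** n per group = 2 × ((1.96 + 0.84)/0.5)² = 62.72, rounded up to 63; total 126; 126/0.9 = 140. The article's 62.8 comes from rounding 31.36 to 31.4. Power at 63 per group is 80.1%. The timing issue does not change this sample size.

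**3. Length of the wait.** Inputs from the article: 70 STAIRS patients and recruitment from October 2022 to June 2024, counted as 21 months. Assumptions: even accrual, an equal split over s sites, groups of m patients, 4.345 weeks per month.

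Rate per site = 70/21/s = 3.33/s per month. First-listed wait = (m − 1)/rate; mean wait = half of that; the last-listed patient waits about zero.

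| Sites (assumed) | Groups of 3: mean / first-listed | Groups of 6 (assumed): mean / first-listed |
|---|---|---|
| 1 | 1.3 / 2.6 weeks | 3.3 / 6.5 weeks |
| 2 | 2.6 / 5.2 weeks | 6.5 / 13.0 weeks |
| 3 | 3.9 / 7.8 weeks | 9.8 / 19.6 weeks |
| 4 | 5.2 / 10.4 weeks | 13.0 / 26.1 weeks |

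**4. What the wait does to a change score.** Let f(t) be the mean score under usual care at time t after randomisation, w the wait, and L the T0-to-T1 interval, taken as equal in both arms. With no treatment effect, and control T0 at time zero:

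difference in change = [f(w + L) − f(w)] − [f(L) − f(0)].

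If f(t) = a + bt, this is bL − bL = 0. If recovery slows over time, the difference is negative (against STAIRS); if it speeds up, positive. The same holds for T2 with a longer L. An allocation reaction r that affects T0 alone in the STAIRS arm adds −r to the difference, with either sign possible.

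**5. Sensitivity, if a net shift did arise.** The shift is in SD units of the change score and is assumed; the documents give no value. With 63 per group the standard error is √(2/63) = 0.178.

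| Assumed shift | Power if it reduces d = 0.5 | Two-sided rejection rate if there is no true effect |
|---|---|---|
| 0 | 80% | 5% |
| 0.05 | 71% | 5.9% |
| 0.10 | 61% | 8.7% |
| 0.20 | 39% | 20.2% |

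**The case against.** The strongest reply is that the wait need not bias anything. T1 and T2 move with T0, so under linear recovery a common shift cancels, as step 4 shows. This stands. A reader might take the score gained during the wait and express it as a share of the planned effect of 0.5; that would compare a shift in level with an effect on change, and it is not supported.

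Control timing is also not documented. One T0 rule is written for all patients, and the figure giving the assessment schedule is not shown. A reader might conclude that controls certainly start at once; the text supports this only as a probable reading.

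The article does not say when patients learn their allocation. In STAIRS, being on a waiting list or invited to a group makes knowledge before T0 very likely. For controls nothing is stated, so it does not follow that every baseline is unblinded. Nor do the documents give attrition during the wait: more missing baselines in STAIRS is plausible but not established.

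Finally, the waits may be short. The minimum of three was chosen to limit them, organisations that do not offer STAIRS refer to a single centre, and the three-month I.ROC recall would damp change over a few weeks.

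None of this removes the core point: by the article's own wording, the STAIRS baseline follows randomisation.

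**Conclusion.** The point holds in this form. In the STAIRS arm, the baseline of the primary change scores is measured after randomisation, after a wait that varies with accrual, and probably with allocation known. In the control arm, T0, T1 and T2 probably fall earlier after randomisation.

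The mean wait is about 1 to 5 weeks with groups of three and one to four equally recruiting sites, and longer with larger groups. The number of sites, the equal split and even accrual are assumptions.

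The size and direction of any bias are unknown. Bias needs non-linear recovery, a reaction to allocation at T0, or unequal loss before T0; the documents quantify none of these. The power and error rates in step 5 show how sensitive the trial would be to a shift; they do not estimate one. Entering T0 as a covariate would not repair the problem, because T0 is itself post-randomisation.

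**What to change.** For patients still to be enrolled, have the existing online T0 questionnaires completed at the consent meeting, before the allocation list is consulted, and use that score as the baseline in both arms.

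Moving T0 is not enough alone, because control letters are counted from T0. Count the letters, T1 and T2 for controls from a start date matched to the STAIRS group dates, so that time since randomisation is comparable between arms. A further I.ROC just before the start can be kept as a descriptive measure.

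For patients already enrolled, report by arm the days from randomisation to T0, T1 and T2 and the number lost before T0, with a sensitivity analysis that takes this timing into account. State in the text when control T0 takes place and when patients learn their allocation.

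Cost: an amendment on assessment timing and some scheduling work to match controls to group dates. The sample size stays at 140. The price is a longer interval from baseline to start of the intervention and a mixed baseline definition for patients already enrolled.

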**Fig. 2 Fig2:**
[figure not shown]
Overview of enrolment, intervention and assessments

### Primary outcome measure

#### Recovery

As STAIRS was developed to support recovery beyond clinical recovery, we chose subjective experienced recovery as the primary outcome measure, which entails both functional and personal recovery. This will be measured with the Individual Recovery Outcome Counter (I.ROC) [50], which is a self-report questionnaire specifically developed to measure the subjective experienced recovery of patients. It focuses on four domains of well-being: (1) home, (2) opportunity, (3) people and (4) empowerment. Each domain consists of 3 recovery aspects, which are described with several keywords and a single question to indicate the level of this aspect in one’s life during the last three months (on a 6-point Likert scale ranging from ‘never’ to ‘always’). The I.ROC sum score of all items (range 12–72) will be used to measure the level of recovery, with higher scores indicating better recovery. The domains focused on by the I.ROC cover both aspects of functional recovery (e.g., everyday skills, movement and being active, social network) and personal recovery (e.g., meaning and life goals, self-esteem, hope for the future). The I.ROC has been shown to have good internal consistency with a Cronbach’s alpha of 0.86 and was found to be a preferred recovery measurement tool by patients compared to two other commonly used recovery measures [50].

### Secondary outcome measures

#### Sample characteristics

A baseline questionnaire consisting of 19 questions related to a patient’s demographic characteristics, education/work status and mental/physical health will be used to gain insight into the sample characteristics. In addition, the gathered information can potentially be used as covariates in analyses to investigate the effects of person characteristics on the effect of STAIRS.

#### Recovery

To be able to compare the results internationally, we will also measure recovery with the Dutch version of the Recovery Assessment Scale – Domains and Stages (RAS-DS) [51]. The RAS-DS is a widely used self-report questionnaire containing 38 recovery-oriented statements focusing on four domains: (1) doing things I value, (2) looking forward, (3) mastering my illness, and (4) connecting and belonging. Patients indicate the level of how much each statement reflects their current lives on a 4-point Likert scale (1 = not true, 4 = totally true). The sum score of all items (range 38–152) will be used, with higher scores indicating better recovery. The RAS-DS has been shown to have a high internal consistency with a Cronbach’s alpha of 0.96 and to be sensitive to change over time [52].

#### Depression-related items

*Depressive symptom severity* will be assessed using the Inventory of Depressive Symptomatology Self Report (IDS-SR) [53], which is a 30-item self-report questionnaire (of which 28 items are scored). Each item focuses on one specific aspect of symptomatology in the last week and is scored on a 4-point Likert scale (0 = no change/difficulties, 3 = strong change/difficulties). The sum score of 28 items (range 0–84) will be used, with higher scores indicating higher levels of depressive symptomatology. The IDS-SR has been shown to have high internal consistency (Cronbach’s alpha is 0.92) [54].

*Depression-related functional impairment* describes the level of impairment patients can experience due to the presence of a mental illness. This will be assessed using the 5-item self-report Sheehan Disability Scale (SDS) [55]. Three out of the five items focus on the level of impairment patients experienced in the past week with regard to their work/school activities, family relationships, and social functioning and are rated on a 10-point Likert scale. The sum score of three items (range 0–30) will be used, with higher scores indicating more disability and impairment due to depressive symptoms.

*Relapse* will be assessed at T2 to determine if a patient has relapsed in the period following treatment. Assessment will be performed by a trained interviewer using the ‘Major Depressive Episode’ (MDE) section of the Dutch version of the Mini International Neuropsychiatric Interview – Simplified (MINI-S) [56], which is a short structured diagnostic interview. The time frame will be adapted to enable assessment of relapse between T1 and T2.

#### Level of control

*Empowerment* is an important aspect of recovery [31, 57] and will therefore be assessed separately using the Nederlandse Empowerment Lijst (NEL) [57]. The NEL is a 40-item self-report questionnaire that focuses on six domains: (1) social support (a respecting and accepting attitude from family and friends), (2) professional help (supportive relationship with caregiver), (3) connectedness (being in contact with others), (4) confidence and purpose (being in charge of one’s own life), (5) self-management (having strategies to cope with difficulties), and (6) caring community (being able to share experiences and having a concerned society). Each item consists of a statement in which participants indicate to what extent this applies to their lives (1 = strongly disagree, 5 = strongly agree). The sum score of all items (range 40–200) will be used, with higher scores indicating higher levels of empowerment. The NEL has been shown to have high internal consistency (Cronbach’s alpha is 0.94) [57].

*Experienced control over one’s life* will be assessed using the Dutch version of the 7-item Mastery scale [58]. In this self-report questionnaire, patients respond to how much they agree with seven statements on a 5-point Likert scale (1 = strongly disagree, 5 = strongly agree), reflecting the extent to which they experience control over what happens in their lives. The sum score of all items (range 7–35) will be used, with higher scores indicating a stronger sense of control. We chose to include this outcome because patients mentioned control over their life as one of the most important aspects when defining what recovery entails to them [59]. The Mastery Scale has been found to have high internal consistency (Cronbach’s alpha is 0.81) [60].

*Self-management skills* will be assessed using the 30-item Self-Management Ability Scale (SMAS-30) [61]. The SMAS-30 is a self-report questionnaire focusing on six domains: (1) taking initiative, (2) self-efficacy, (3) investment behaviour, (4) positive frame of mind, (5) variety and (6) multifunctionality. Each domain consists of five questions that are scored on either a 6-point Likert scale (1 = never, 6 = very often; for four domains) or a 5-point Likert scale (1 = absolutely yes, 5 = absolutely no; for two domains). After transformation, each domain has a range of 0–20. The sum score of all domains (range 0–100) will be used, with higher scores being indicative of better self-management skills. The SMAS-30 has been found to have high internal consistency (Cronbach’s alpha is 0.90) [62]. Self-management will be assessed because this has been found to be an important skill that contributes to both the prevention of relapse and coping with the day-to-day consequences of (residual) depressive symptoms [63].

### Cost-effectiveness

*Direct and indirect costs* (medical costs and productivity loss) associated with the psychosocial problems caused by depression will be assessed using the 26-item Treatment Inventory of Costs in Patients with psychiatric disorders (TiC-P) [64], which includes the 11-item Short Form Health and Labour Questionnaire (SF-HLQ) [65]. The first part of the TiC-P contains 15 questions that assess contacts with a range of healthcare providers and medical specialists (yes/no; followed by an assessment of the number of visits). The second part focuses on work loss for both paid and unpaid work, and reduced efficiency at work.

*Quality of life* will be assessed using the 10-item Recovering Quality of Life (ReQol) [66]. In this self-report questionnaire, seven domains are assessed: (1) activity, (2) belonging and relationships, (3) choice, control and autonomy, (4) hope, (5) self-perception, (6) wellbeing and (7) physical health. Each domain is covered by one or two items that are scored on a 5-point Likert scale (0 = none of the time, 4 most or all of the time; negatively worded questions will be scored from 4 to 0). The sum score of all domains (range 0–40) will be used, with higher scores indicating higher levels of recovering quality of life. The Dutch version of the ReQol has a high internal consistency (Cronbach’s alpha is 0.90) [67]. We chose the ReQol because this questionnaire is specifically developed to incorporate patient perspectives on all relevant aspects concerning recovery and because it has better responsiveness: a moderate standardized response means [SRMs] was previously found for the ReQol versus small SRMs for the EQ-5D [66]. The Recovering Quality of Life – Utility Index (ReQoL-UI) will be used to convert the ReQoL sum score into a preference-based index score that is used to calculate QALYs [68].

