### Statistical analysis

#### Power calculation

Based on previously conducted meta-analyses on the effect of psychosocial interventions [71], behavioural activation treatment [72] and supported internet-based treatment [73] on the social functioning of patients with depression, a medium effect size is expected. The sample size estimation for the RCT was based on a Cohen’s d of 0.5, a *p*-value cut-off (alpha) of 0.05 (Z_alpha_ 1.96) and a power (1-beta) of 80% (Z_beta_ 0.84). The following calculation was used to obtain the number of needed participants per group (n_gr_): N_gr_ = (SD_gr1_ + SD_gr2_/ratio) * ((Z_alpha_ + Z_beta_)/d)^2^, where the ratio between the two groups’ sample sizes (n_gr1_/n_gr2_) was set to 1 (equal group sizes). This calculation resulted in (1 + 1/1) * ((1.96 + 0.84)/0.5)^2^ = 2 * 31.4 = 62.8) an estimated 63 participants needed per group (total sample size = 126). With an expected dropout rate of 10%, we arrived at a total required sample size of 140 ((126/9)*10), with 70 participants per treatment group.

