
### Economic evaluation

As part of the RCT, the cost-effectiveness of STAIRS will be evaluated. Analyses will be performed using the societal perspective, as we are interested in all relevant costs, including direct costs (healthcare costs) and indirect costs (productivity loss). Healthcare costs will be calculated by multiplying the healthcare resource use (general practitioner visits, hospital days, etc.) during the last three months, as assessed with the TIC-P, by their reference cost prices as described in the guideline for economic evaluation [79]. The costs for delivering the intervention will be calculated by multiplying the number of hours spent by both trainers per group by the average hourly wage of a clinician and an expert by experience according to the collective employment agreement for Dutch mental healthcare and dividing this by the average number of participants per group. Productivity loss will be calculated by summing the costs of absenteeism and presenteeism. Absenteeism will be calculated using the friction cost method by multiplying the lost working hours in the last month by an average hourly wage. The percentage of work loss due to presenteeism will be calculated by multiplying the percentage of lost productivity while at work (indicated by patients on a 0–10 range) by the number of hours affected. Although productivity loss is expected to be less important in the studied population, as unemployment is relatively high, data on productivity loss will be collected anyway because the intervention under study is also targeted at regaining satisfactory functioning in a (paid or unpaid) job again. All reference cost prices and average hourly wages will be corrected based on inflation rates to represent realistic costs for the present time.

The cost-effectiveness of CAU + STAIRS versus CAU + basic psychoeducation will be analysed by calculating the incremental cost-effectiveness ratio (ICER). For this, the difference in total costs of both interventions (healthcare and productivity costs between T0 and T1/T2, plus the costs of deploying the intervention) will be divided by the difference in effect of both interventions. The incremental costs will be reported per QALY gained as well as per point gained on the I.ROC to provide insights into both the cost-utility and the cost-effectiveness of the STAIRS program.

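### The article names the ReQoL sum score as the input to the utility index, and a total cannot carry the item-level preference weighting that the index is meant to supply

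*Protocol article*

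**What the plan says.** The Cost-effectiveness section, under measurements, introduces the ten-item ReQoL as the quality-of-life questionnaire. On scoring it says: "Each domain is covered by one or two items that are scored on a 5-point Likert scale". It then defines one score: "The sum score of all domains (range 0–40) will be used, with higher scores indicating higher levels of recovering quality of life".

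The same paragraph ends with the step to utilities. The ReQoL-UI "will be used to convert the ReQoL sum score into a preference-based index score that is used to calculate QALYs".

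The Economic evaluation section uses those QALYs as one of two effect measures in the ICER: "The incremental costs will be reported per QALY gained as well as per point gained on the I.ROC". Nowhere does the article say that item responses are valued, and nothing later in the text changes the stated input.

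**The concern.** A preference-based index attaches values to described states, that is, to particular answers on particular items. Once the answers are added with equal weight, the state can no longer be recovered from the result. The sentence therefore promises preference weighting and names an input to which item-level weights cannot be applied. This follows from what such an index is and does not depend on the actual ReQoL-UI weights.

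At stake is the cost-utility result. Lower cost per QALY is one of the hypotheses listed at the end of the Background, and the Economic evaluation section expects the ICER to fall below a national threshold. A total and an item-based index can part company when a treatment acts on some domains more than others, which is plausible here. The STAIRS session themes in the Interventions section include self-image, meaningfulness and connection with others. Physical health, one of the seven ReQoL domains, is not listed as a session theme.

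**Working it through.** **1. The stated score.** Inputs from the Cost-effectiveness section: 10 items, each scored 0 to 4. With weight 1 per item the maximum is 10 × 4 = 40 and the minimum is 0. This reproduces the stated range 0–40, so the score is an unweighted sum.

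**2. What a conversion of the sum can do.** Write S for the total and f for any conversion, linear or not. If two patients have S = 20, both receive f(20), whatever their answers. There are at most 41 possible utilities, for totals 0 to 40. The response patterns number 5^10 = 9,765,625. The coefficient of x^20 in (1 + x + x² + x³ + x⁴)^10 is 856,945, the number of patterns that share the total 20. These counts show what a sum can discard. They do not measure bias.

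**3. Illustration for two patients, with assumed weights.** The article gives no weights, so the following are assumptions: an additive index scaled 0 to 1, using all ten items, with five items weighted r times the other five. Patient A scores 4 on each heavier item and 0 on each lighter one. Patient B is the reverse. Both total 20. Then utility A = 5r/(5 + 5r) = r/(1 + r), and utility B = 1/(1 + r).

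| r | A | B |
|---|---|---|
| 1 | 0.50 | 0.50 |
| 2 | 0.67 | 0.33 |
| 4 | 0.80 | 0.20 |

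A conversion of the sum gives A and B one shared value in every row. Under this index nothing is lost only at r = 1, where all items count equally.

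**4. The same assumptions for a group difference.** Take a mean difference of one point on the total, falling wholly in one block. Each point is worth 1/[4(5 + 5r)] in the lighter block and r times that in the heavier block. A straight-line conversion of the sum gives 1/40 = 0.025 in either case.

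| r | All in lighter block | All in heavier block | From the sum |
|---|---|---|---|
| 1 | 1/40 = 0.025 | 1/40 = 0.025 | 0.025 |
| 2 | 1/60 = 0.017 | 2/60 = 0.033 | 0.025 |
| 4 | 1/100 = 0.010 | 4/100 = 0.040 | 0.025 |

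The error can go either way. It vanishes when the effect is spread evenly over the two blocks. For r = 2, half a point in each block gives 0.5/60 + 0.5 × 2/60 = 0.025. The table shows the mechanism and is not an estimate for this trial.

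**The case against.** The best reply is that this is loose wording. The trial adopts a named external index, with a cited source, rather than devising its own conversion. If that index is scored from item answers, an analyst who applies it will need them, and the harm will not arise. That is a fair reading and it limits the point: a reader might infer that the authors have decided to map totals to utilities, but the article does not establish that. What remains is that the sentence names the wrong input. A later analysis plan can fill in what an article leaves out, but here the article states a rule.

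Other stronger inferences also go too far:

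- *The utilities would be just the quality-of-life score rescaled.* Not necessarily. Mapping a total to utilities is a recognised, less precise technique, and the map can be non-linear and anchored to preferences. What it must lose is the variation among patients with the same total.
- *The pattern counts show a large error.* They do not. The article reports a Cronbach's alpha of 0.90 for the Dutch version, so items tend to move together and many patterns will be rare. The article also does not say how many of the ten items enter the index.
- *Defining a 0–40 sum is itself a mistake.* The sentence "The sum score of all domains (range 0–40) will be used" is a proper definition of the quality-of-life outcome, in line with the other scales.
- *The plan imputes the sum.* The Data analysis section says only that missing values are imputed 20 times by fully conditional specification. It does not give the level, and an article may leave that to the fuller document.

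**Conclusion.** The point stands as a misstated scoring rule. As written, the article feeds an equal-weight total into a preference-based index, and no function of that total can apply item-level preferences. Followed literally, it would give incorrect utilities for the cost-per-QALY ratio.

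The size of the effect on the QALY difference is unknown. It depends on the index weights and on how any treatment effect is spread over the items, and the article gives neither. The reach is narrow: the I.ROC primary outcome, the sample size of 140, the clinical secondary outcomes and the cost per I.ROC point are untouched. The conclusion rests on one general premise, that a preference-based index values answers to particular items, and on reading the sentence as written.

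**What to change.** Replace the clause on converting the sum score with a statement that the ReQoL-UI is scored from the individual ReQoL item responses at T0, T1 and T2, using its published value set, and that the resulting index is used for QALYs. Say that the 0–40 sum serves only as the quality-of-life outcome. Where ReQoL answers are missing, impute at a level that permits this scoring, either the items or the index itself. This makes the scoring rule workable and does not correct a stated imputation rule.

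The cost is one sentence. The questionnaire already collects the item responses, so no new data, visits or participants are needed, provided the item responses are kept in the dataset.
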